## Abstract

Background: Neurocognitive impairment is a prominent characteristic of bipolar disorder (BD), linked with poor psychosocial functioning. This study’s purpose is to evaluate the effectiveness of functional remediation (FR) in enhancing neurocognitive dysfunctions in a sample of remitted patients with diagnosis of BD in comparison to treatment as usual—TAU. To quantify the neurocognitive damage, the Brief Assessment of Cognition in Affective Disorders (BAC-A) will be used, and the overall psychosocial functioning will be measured with the Functioning Assessment Short Test—FAST. Methods: The randomized, rater-blinded, controlled study will include two arms (1:1) encompassing 54 outpatients with diagnosis of BD-I and BD-II, as defined by the DSM-5 criteria. In the experimental phase, remitted patients aged 18–55 years will be involved. At the baseline, at the end of intervention and at the 6-month follow-up, patients will be evaluated using clinical scales (Young Mania Rating Scale (Y-MRS) and Hamilton Depression Rating Scale (HAM-D)). Neurocognitive measurements and psychosocial functioning will be valued, respectively, with BAC-A and FAST. Discussion: The primary expected outcome is that following FR intervention, patients will exhibit improved cognitive abilities and psychosocial outcomes compared to the participants in the TAU group. It is now recognized that neurocognitive deficits are potential predictors of functional outcome in patients with BD. In recent years, there has been a growing interest in the implementation of interventions that, in addition to symptomatic remission, are also aimed at neurocognitive dysfunctions in order to achieve a recovery of psychosocial functioning.

## 1. Background

Bipolar disorder (BD) is a chronic, recurrent and disabling psychiatric disorder [1,2]. It is characterized by the presence of episodes of mania, hypomania and depression, with euthymic intervals [3], and it is classified as a major medical cause of disability [4], affecting approximately 2.4% of the world population [5].

Cognitive dysfunction is a major feature of BD that is strongly associated with patients’ functional outcome, and several meta-analyses have reported that the most affected cognitive domains are sustained attention, verbal memory and executive functions [6,7,8]. Cognitive deficits in BD are important determinants of overall psychosocial functioning since they are present during the euthymic phases [9,10,11]; in fact, patients frequently experience persistent residual symptoms, cognitive impairment, problems in psychosocial functioning and poor quality of life even outside of mood episodes [12,13]. Given the close link between neurocognition and psychosocial functioning [14], the main target of intervention is complete functional recovery, with a focus on current well-being; it is now established that the quality of life depends not only on clinical remission but also on functional outcomes [15].

As concerns the great clinical variability observed in BD, a growing body of evidence confirms a significant heterogeneity in cognitive performance [16,17,18]. Recent evidence attests the existence of subgroups of patients characterized by different levels of cognitive functioning: some patients show normal cognitive performance, some present a moderate cognitive impairment and others suffer from severe neurocognitive deficits [16,17,19,20,21,22]. In fact, 40% of patients diagnosed with BD show severe deficits in various cognitive domains and 30% show moderate and specific difficulties, while others are cognitively intact [8,16]. As regards psychosocial functioning, some evidence also showed a relationship with social cognitive performance [23].

Considering that cognitive deficits could represent an important target of intervention as they worsen the functional outcome, identifying a correct trajectory of intervention and personalizing programs for the treatment of cognitive difficulties, thus leading to an improvement in functioning, quality of life and well-being, represent central objectives for patients with BD [13]. Although pharmacological treatment is essential in the clinical management of BD and represents the basis for treatment success [24], the need for non-pharmacological interventions is increasingly emerging. Given that, as often happens in BD, the prognosis may worsen due to poor medication adherence [25], an integrative approach could represent a valid solution.

BD involves considerable therapeutic complexity; to implement a successful treatment focusing on clinical remission and on functional recovery, aiming at the patient’s well-being and a better quality of life is advisable [13,15]. A growing body of evidence confirms the importance of integrated treatments that include psychosocial interventions and that facilitate the consolidation of symptomatic improvements induced by drug treatment, thus increasing the quality of life and contributing to a general recovery of psychosocial functioning [26].

Cognitive remediation (CR) is an evidence-based intervention originally designed for patients diagnosed with schizophrenia, with an effectiveness profile that is now well-established and supported by a solid body of evidence [27,28,29]. It is currently the psychosocial intervention with the highest degree of recommendation for treating cognitive impairment in schizophrenia according to recent international guidance [30].

It has also recently received new attention for its potential as an effective treatment for people living with BD, with an adaptable program; comparative studies have reported a similar level of heterogeneity of cognitive impairment in schizophrenia and BD, and considering the significant overlaps between the neurobiological and clinical data available, similar trajectories and common deficits can be observed [31].

However, a current and noteworthy criticism is that CR interventions lack specificity for BD, as the profiles of cognitive deficits in BD and schizophrenia are similar but not identical and are generally less severe in BD [32,33]. Therefore, it appears that programs designed for people living with schizophrenia are perceived as too simple for patients with BD, thereby invalidating their participation and causing scarce adherence [34]. Hence, there is a need to implement more specific interventions for BD that take into account the cognitive heterogeneity of this condition. Particular attention should also be given to the cognitive subgroups with the aim of developing neurocognitive approaches suitable for the different needs expressed.

A stimulating debate has recently been launched with the participation of numerous BD experts, focusing on the real usefulness of a CR intervention that is specifically designed for BD [35,36,37]. Although it is recognized that many patients do not present objectively defined cognitive impairment, it is important to keep in mind that some subjects complain of difficulties that are clinically relevant but are configured as subjective cognitive disorders [36]. According to Burdick and colleagues, this could reflect the presence of unresolved mood symptoms, reversing the idea of interventions aimed solely at cognitive improvement: this issue further highlights the need to implement new interventions for BD [36]. Experts from the International Society for Bipolar Disorders (ISBD) have identified a number of methodological challenges for designing treatments targeting cognitive disorders in BD with the aim to achieve functional recovery [8,38].

Given that, to date, the link between neurocognitive and real-world functioning is not completely clear for people living with BD, it is necessary to further investigate the functional implications deriving from the efficacy of the treatment on cognition. It is worth mentioning that the methodological recommendations for cognition trials provided by the Cognition Task Force from the ISBD encourage the inclusion of a functional measure as a co-primary key measure of functional change [38]. In this regard, in the last decade, there has been a proliferation of psychological interventions specifically aimed at the recovery of psychosocial functioning in BD, with an emphasis on cognitive functioning [37,39,40,41].

In particular, an interesting and innovative program is functional remediation (FR), an intervention specifically developed by the Bipolar and Depressive Disorders Unit of the Hospital Clinic of Barcelona that aims to ameliorate functional outcomes by targeting neurocognitive difficulties in euthymic patients diagnosed with BD [39]. FR is an intervention delivered in a group format and based on the neurocognitive behavioral model that aims to enhance neurocognition and functional impairment associated with BD. It is based on the concept that improving cognitive performance in BD could produce consistent gains in psychosocial functioning and draws upon recent evidence showing that CR and cognitive behavioral interventions are feasible and effective in producing significant cognitive gains in people living with BD [39,40,41,42,43,44,45,46].

FR efficacy was explored in a multicentric, randomized, rater-blind trial, which showed an improvement in general psychosocial functioning, especially in the interpersonal and occupational domains [39]. FR has been shown to be effective in enhancing psychosocial functioning in both BD I and BD II [47,48], and the durability of its efficacy was attested at the one-year follow-up, also showing a persistent improvement in verbal memory [12].

However, more scientific evidence is currently required to replicate the results of FR effectiveness on functional outcomes in clinical settings and to explore its effectiveness on secondary outcomes such as cognitive performance and, in particular, social cognition performance. Moreover, moderators and predictors of response remain to be assessed.

### Trial Aims and Objectives

The present project aims to evaluate the efficacy of FR in improving psychosocial functioning, cognitive deficits and the quality of life in a sample of euthymic patients diagnosed with BD. This intervention will be compared with a control condition: a group of participants will follow a treatment as usual (TAU) program that includes only pharmacological treatment according to good clinical practice.

The primary objective measure is the score on the Functioning Assessment Short Test (FAST) from the baseline to the endpoint. The hypothesis is that an integrated treatment (FR + TAU) may be more effective than the standard treatment (TAU) in improving psychosocial functioning in BD. We hypothesize that patients involved in an FR group will show improvements in overall psychosocial functioning compared to patients included in the control group (TAU).

One secondary objective is to evaluate whether integrated treatment (FR + TAU) can allow a more effective response in improving neurocognitive and socio-cognitive performance and subthreshold affective symptoms compared to standard treatment (TAU). A further secondary objective is the identification of possible sociodemographic, clinical, cognitive and functional predictors of clinical, cognitive and functional responses in the two groups of patients.

## 2. Methods

### 2.1. Trial Governance

This trial is currently registered with ClinicalTrials.gov (NCT04577508) and has been approved by the local Ethics Committee (reference NP 3976, NP 3977 and NP 3978); all the procedures comply with the ethical principles of the Declaration of Helsinki [49] and are of good clinical practice [50]. The Consolidated Standards of Reporting Trials (CONSORT) guidelines [51] will be followed.

### 2.2. Trial Design and Setting

This is a pilot randomized and rater-blind controlled trial involving 54 clinically stable subjects with a diagnosis of BD type I or II and comprising a 6-month intervention phase and a 6-month follow-up period. Study participants will be assigned to either FR in addition to TAU (n = 27) or TAU alone (n = 27). Clinical assessments will be conducted at baseline, post-treatment and after a follow-up of 6 months (shown in Figure 1).

### 2.3. Participants

Study participants will be recruited from outpatient services or semi-residential or residential care within three different operative units of the Department of Mental Health and Addiction Services of ASST Spedali Civili, Brescia, Italy. In this setting, in line with clinical guidelines [51], standard treatment for subjects with a diagnosis of BD consists of pharmacological treatment and individual case management. The trial will not directly impact concomitant routine treatment. However, patients receiving psychosocial interventions potentially active on cognition will be excluded from the study.

#### 2.3.1. Inclusion Criteria

Eligible participants will be fully informed about the study procedure and included only if providing written informed consent. They will be required to meet the following inclusion criteria: (a) age between 18 and 55 years; (b) education level of ≥8 years; (c) diagnosis of BD type I or II as referred from treating psychiatrist and confirmed at recruitment using the Structured Clinical Interview for Disorder for DSM-5, Clinical Version (SCID-5-CV) [52]; (d) clinical re0mission according to DSM-5 criteria (no mood episodes for ≥2 months) [53]; (e) euthymic phase at baseline assessment (defined as scoring both ≤6 points on the Young Mania Rating Scale (Y-MRS) [54] and ≤8 points on the Hamilton Depression Rating Scale (HAM-D)) [55]; (f) moderate to severe degree of functional impairment (defined as a score of ≥18 points on the Functioning Assessment Short Test (FAST)) [56]; (g) adequate mastery of Italian language, spoken and written.

According to these criteria, participants will not be pre-screened for neurocognitive impairment since the main focus of FR is functioning rather than cognition, and this program is primarily (though not exclusively) aimed at promoting psychosocial functioning among patients with significant impairment in occupational and interpersonal domains [15].

Concomitant medications will be kept stable as much as possible throughout the trial in order to reduce confounding effects. For patients receiving lithium therapy, the serum dose will be monitored over time and maintained within the therapeutic range. No major restrictions will be applied in terms of medication doses or compounds in order to not affect trial feasibility and the generalizability of the results; however, subsequent analyses are going to include the investigation of the potential influence of these parameters on treatment effect.

#### 2.3.2. Exclusion Criteria

Exclusion criteria for the present study are as follows: (a) diagnosis of intellectual disability (DSM-5 criteria); (b) comorbidity with neurological or other medical diseases possibly affecting cognitive performance or the execution of neuropsychological tests (e.g., epilepsy, history of moderate to severe brain injury, current uncontrolled thyroid disease, unstable medical illness); (c) any psychiatric comorbidity (including anxiety disorders, active alcohol/substance abuse or history of abuse in the 3 months prior to screening); (d) electroconvulsive therapy within the past year; (e) pregnancy; (f) inability to provide informed consent/withdrawal of consent.

### 2.4. Procedures

#### 2.4.1. Screening and Randomization Phase

The enrolment phase will last six months. A systematic recruitment strategy will be applied, targeting all patients diagnosed with BD and receiving outpatient care. Eligible subjects will be identified through clinical documentation systems and informed of the study by their treating psychiatrist; they will be then approached by a study investigator to further discuss the study procedures. Only patients giving their consent will be administered the screening interview (shown in Figure 2).

#### 2.4.2. Allocation and Blinding

Patients fulfilling all inclusion criteria will be randomized to the two parallel groups by a researcher not involved in the subsequent trial procedures, using a computer-based system (1:1 ratio). The allocation sequence will not be based on any stratification procedure, and all the details related to randomization will be kept locked following treatment allocation (Figure 1).

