### 2.5. Treatment as Usual

Subjects enrolled in the TAU group will receive the prescribed pharmacological treatment according to the guidelines and good clinical practices envisaged for BD [50]. Participants recruited to the TAU group will not receive FR intervention.

Subjects enrolled and belonging to both groups will have access to other evidence-based treatments for bipolar disorder, according to clinical decisions.

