## 3. Measurement

### Statistical Analyses

All the analyses will be carried out using SPSS version 14.0 for Windows (SPSS Inc., Chicago, IL, USA, 2005).

Improvements in psychosocial functioning and cognitive performance will be assessed using effect size estimates obtained from within- and between-group differences at repeated measures analyses of variance (rm-ANOVAs). In case of attrition rate > 20%, a mixed model will be employed, under the missing at random (MAR) assumption. Regarding clinical symptoms, treatment effects will be compared among patients with and without residual symptoms (≥1 on Y-MRS, ≥3 on HAM-D) using t-tests.

Given the small sample size, the investigation of potential predictors of response through regression analyses should be considered largely explanatory. However, some regression analyses will be performed as deemed important in light of the feasibility nature of this trial; variables of interest will include participants’ age, duration of illness, baseline functioning, baseline cognitive performance and change in cognitive performance as well as potentially emerging predictors of dropout. In fact, participants leaving the study early will be compared with those completing all study procedures in terms of demographic and clinical variables using inferential statistics to assess potential moderators.

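### Allocation ignores the three operative units: a minor, cheaply avoided risk of chance imbalance in a trial of 54

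*Protocol article*

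**What the plan says.** Section 2.4.2 of the protocol article describes a computer-generated 1:1 allocation run by a researcher who has no later role in the trial. It adds: "The allocation sequence will not be based on any stratification procedure". Section 2.2 fixes the arms at 27 and 27.

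Section 2.3 says that patients are "recruited from outpatient services or semi-residential or residential care within three different operative units" of one department. It gives a single account of usual care for the whole setting: "standard treatment for subjects with a diagnosis of BD consists of pharmacological treatment and individual case management". Section 2.5 adds that patients in both arms "will have access to other evidence-based treatments for bipolar disorder, according to clinical decisions".

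The Statistical Analyses section names a repeated-measures ANOVA, replaced by a mixed model if attrition exceeds 20%. The sample size section powers the group × time interaction on FAST. Neither names operative unit as a factor. It is also absent from the patient characteristics listed in section 2.7 and from the variables of interest for the exploratory regressions.

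**The concern.** Unit is known for every patient before allocation, so balancing on it costs almost nothing. The article rules that out expressly. In a trial of 54, balance over three units is then left to chance.

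Two things are at stake, both modest:

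- **Credibility of the single realised allocation.** If one unit is over-represented in one arm, any unit difference in how FAST changes over the year is mixed with the effect of functional remediation. With no adjustment fixed in advance, an imbalance that readers can see invites post hoc modelling.
- **Precision.** Any part of the variation in FAST change that unit explains stays in the error term.

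Unit could matter for change. Care beyond the standard is left to clinical decision, and patients come from outpatient, semi-residential and residential care. The article does not say that it does matter.

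**Working it through.** **1. The plan's own sample size.** Inputs from the sample size section: f = 0.25, alpha 0.05, power 95%, two groups. Section 2.6 gives three assessments. A correlation of 0.5 between assessments and sphericity are assumed, since the article states neither.

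- λ = f² · N · m / (1 − ρ) = 0.0625 × 44 × 3 / 0.5 = 16.5
- df1 = 2; df2 = (44 − 2) × 2 = 84
- Power = 95.6%, and 44 is the smallest even N that reaches 95%.
- Attrition: 44 / 0.8 = 55, against the stated 54.

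The figure of 44 reproduces. It assumes no stratification and no unit term, so leaving unit out does not reduce the planned power.

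**2. Chance imbalance over units.** With 27 per arm and unit sizes s1, s2, s3, the probability that a, b and c patients of the three units fall in one arm is C(s1,a) · C(s2,b) · C(s3,c) / C(54,27). Unit sizes are assumed.

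| Assumed unit sizes | Some unit split 2:1 or worse | Some unit's share differs between arms by ≥ 20 points | by ≥ 30 points |
|---|---|---|---|
| 18/18/18 | 31% | 31% | 2% |
| 27/18/9 | 54% | 21% | 3% |
| 34/10/10 | 49% | 23% | 1% |

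An unrestricted 1:1 draw would give 56% for 18/18/18 and 67% for 27/18/9, but the article gives 27 per arm, so the fixed-split figures are the relevant ones. The 54% comes mostly from the nine-patient unit, which splits 6:3 or worse in 47% of draws. The 27-patient unit splits 2:1 or worse in 3%.

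**3. What an imbalance could do to the FAST comparison.** The powered test is group × time. A constant unit difference in FAST level is present at every assessment and cancels in that contrast. Only unit differences in *change* count.

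Suppose three units of 18 have mean changes of −d, 0 and +d:

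- Sum of squares = 36d², so S² = 36d² / 53.
- SD of the chance arm difference = √(S² × 4/54) = 0.224d.
- d = 5 points: SD 1.1; the arms differ by 2 points or more in about 7% of allocations.
- d = 8 points: SD 1.8; 2 points or more in about 24%.

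These are strong assumptions. They put the extreme units 10 or 16 points apart in change on a 0–72 scale. The between-unit variance is 2d²/3. With an assumed within-unit SD of 8–12 points, unit would explain about 10–21% of the variance at d = 5 and 23–40% at d = 8.

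**4. Precision gained by stratifying and adjusting.** If unit explains a share R² of the variance in FAST change, the variance of the treatment comparison is multiplied by 1 − R² and the standard error by √(1 − R²).

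| R² (assumed) | Cut in standard error | Power at N = 44 |
|---|---|---|
| 0 | none | 95.6% |
| 1% | 0.5% | 95.8% |
| 5% | 2.5% | 96.4% |
| 10% | 5% | 97.2% |

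This is before the small loss of degrees of freedom, which leaves essentially no gain at 2% or less. At 5–10% the gain is worth 0.05 × 54 = 2.7 to 0.10 × 54 = 5.4 patients.

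**5. Adjusting without stratifying.** When unit is not balanced by design, adjustment for it inflates the variance by a factor of roughly 1 + 2/(N − 4) on average: 1.04 at N = 54 and 1.05 at N = 44. It helps only when (1 − R²) times that factor falls below 1, so R² must exceed about 4–5%.

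**The case against.** The strongest reply is that unstratified allocation is a legitimate choice, openly reported, in a trial that calls itself a pilot. No stated figure is wrong and nothing in the article is contradicted. That stands, and it is why the point is minor.

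A reader might also draw four stronger conclusions that the article does not support:

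- **That the treatment comparison is biased or the test invalid.** Unstratified randomisation is unbiased in expectation and the type I error holds. The risk concerns one realised allocation.
- **That precision or planned power is lost.** The sample size was derived without unit. Only a possible small gain is forgone, and only if unit predicts FAST change.
- **That usual care differs by unit.** The units belong to one department and section 2.3 gives one common standard treatment. Section 2.5 allows discretion but does not tie it to unit. A difference is possible, not documented.
- **That the plan excludes unit from the model.** The article names no such term, but a condensed article may leave covariates to the full protocol or the analysis plan. The point therefore rests on the express statement about stratification, not on the silence about the model.

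The imbalance percentages also need care. A 2:1 split in a very small unit barely moves the arm comparison, and differences of 30 points or more in a unit's share are rare (about 1–3%). What survives is that a moderate imbalance is quite likely and that preventing it is almost free.

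**Conclusion.** The point holds as a cheap improvement of minor weight. Allocation is expressly unstratified over three known units. Under the assumed unit sizes, about 31–54% of allocations with 27 per arm would split at least one unit 2:1 or worse. The stated sample size and the error rate are unaffected.

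The benefit of stratifying and adjusting depends on a quantity that the article does not give, the share of variance in FAST change explained by unit. It is about 5–10% of variance if that share is 5–10%, and essentially nothing at 2% or less. The 5- and 8-point scenarios apply only to unit differences in FAST change. Protection against a visible imbalance is gained in any case.

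**What to change.** **If recruitment has not begun:** generate the 1:1 sequence in randomly permuted blocks of varying, undisclosed size within each of the three operative units. Include unit and its interaction with time in the FAST model. The interaction is needed because a unit main effect alone leaves the error term of the group × time test unchanged.

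**If recruitment has begun:** keep the sequence. Prespecifying the unit term, before any outcome is seen by arm, is then optional, since it helps only if unit explains more than about 5% of FAST change.

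**Cost:** a setting in the existing computer-based system and a sentence in the analysis text. The model gives up two between-subject degrees of freedom; with the interaction, the within-subject error at N = 44 goes from 84 to (44 − 4) × 2 = 80. Allocation within a unit becomes slightly more predictable, which varying block sizes limit. Incomplete last blocks may leave the totals slightly off 27:27. No extra patients, visits or staff are needed.
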